## Abstract

**Background:**

Primary dysmenorrhea (PD) is a common gynecological disorder that significantly affects women’s work and personal lives, especially in acute episodes when immediate pain relief is often needed. The objective of this study is to evaluate the immediate analgesic effect of acupuncture for acute PD within 10 min.

**Methods:**

This is a randomized sham-controlled clinical trial involving 80 participants with acute PD who will be randomized in a 1:1 ratio into the Acupuncture group and the Sham acupuncture group. Each participant will receive 10 min acupuncture session. For participants in the Sham acupuncture (SA) group, the Park Sham Acupuncture Device (PSD) and blunt needles will be used to simulate treatment without skin penetration. The visual analog scale (VAS) will be evaluated before treatment and at 0–1, 2, 4, 6, 8, and 10 min after treatment. The primary outcome is the effective analgesia rate after 10 min of acupuncture. Secondary outcomes include effective analgesia rate at other time points (0–1, 2, 4, 6, and 8 min), VAS, blinding assessment, and the treatment effectiveness expectations scale. Adverse events during each treatment period will be collected and recorded. All outcomes will be analyzed on an intention-to-treat. The recruitment for this study is expected to be completed between May 1, 2024, and September 1, 2025.

**Discussion:**

The primary need of patients with PD is the immediate relief of pain. This study aims to investigate the immediate analgesic effect of acupuncture on acute PD. The results of this study will provide a rapid and reliable clinical basis for the use of acupuncture in the treatment of PD, potentially offering a non-pharmacological alternative for pain management that could reduce reliance on medications and their associated side effects.

**Clinical trial registration:**

Identifier ChiCTR2300070826. This study has been registered at the Chinese Clinical Trial Registry (https://www.chictr.org.cn).

## Introduction

Primary Dysmenorrhea (PD) is a functional pain disorder without organic pathology, characterized by severe cramping lower abdominal pain during or before menstruation (1). It has been a common gynecological condition that troubles women, and globally, the prevalence among women of reproductive age ranges from 16 to 94% (2). Severe cases may be accompanied by additional symptoms such as nausea, vomiting, diarrhea, weakness, and even fainting (3). Moderate to severe acute PD can be debilitating for women of childbearing age, reducing their quality of life, affecting their productivity at work and school (4), and potentially causing additional psychological burdens (5, 6). In Europe, PD results in the loss of 3.6 million quality-adjusted life years annually, which is comparable to the impact of chronic conditions such as asthma or chronic migraines (7).

Non-steroidal anti-inflammatory drugs (NSAIDs) and hormonal drugs are currently the first choice for the clinical treatment of acute PD (8). However, these drugs are accompanied by some side effects, such as the potential for digestive disorders, headaches, and drowsiness. In general, analgesic drugs begin to take effect after about 15 min (9), and some medications used for treating acute PD may have subtle or delayed effects (10). The primary and urgent need for patients is immediate relief from pain during each PD episode. However, the dependence on medications and their side effects leads to hesitation in medication choices. Therefore, developing rapid, efficient, and low-risk treatment methods is the focus of current research.

With the increasing research on nonpharmacologic therapies, acupuncture has become a widely accepted approach in pain management (11, 12), demonstrating positive and significant effects in alleviating acute pain (13–19). Acupuncture has also shown clinical effectiveness in treating acute PD (18, 19), but there is a lack of rigorously standardized randomized controlled trials (RCTs) to support this. Therefore, we have designed this RCT to investigate the immediate analgesic effects of a 10-min acupuncture intervention in acute PD. The 10-min observation period is selected because prior studies suggest that acupuncture’s peak analgesic effect typically occurs within 5–10 min of treatment initiation (20–22). This duration also balances clinical feasibility and patient compliance, avoiding the fatigue and inattention associated with longer sessions.

## Materials and methods

### Trial strategy

The study protocol is designed following the Declaration of Helsinki principles and the Standard Protocol Items: Recommendations for Interventional Trials guidelines (SPIRIT 2013) (23). Figure 1 shows the SPIRIT schedule of enrolment, intervention, and assessments. Figure 2 shows the flow chart of the study design is shown in.

**Figure 1 fig1:**
[figure not shown]
Study schedule for data measurements.

**Figure 2 fig2:**
[figure not shown]
Flowchart of the study design.

This study has been approved by the Ethics Committee of the Second Affiliated Hospital of Yunnan University of Chinese Medicine (approval number: 2022–010). The study was registered on the Chinese Clinical Trial Registry (ChiCTR2300070826).

### Recruitment and informed consent

This is a randomized controlled trial (RCT) aimed at evaluating the immediate efficacy of acupuncture in the treatment of acute PD. The study will be conducted at the Second Affiliated Hospital of Yunnan University of Traditional Chinese Medicine, with a planned recruitment of 80 participants diagnosed with PD. A public recruitment advertisement for this study will be designed to recruit the participants online or offline channels, such as the websites, and WeChat public account. Upon meeting the inclusion criteria and expressing willingness to take part in this study, participants will be required to provide written informed consent prior to the commencement of the study (Appendix 1). During the baseline period, participants will be asked to provide information regarding menstrual cycle characteristics (e.g., cycle length, regularity, duration), baseline pain threshold, prior analgesic use, and prior acupuncture experience. These variables will be collected for exploratory analysis of potential confounding effects. Participants retain the right to withdraw from the study at any point, and their personal data will be solely utilized for medical research purposes.

### Eligibility criteria

To be enrolled in this study, the following eligibility criteria, assessed at screening, will be met:

### Inclusion criteria

Participants will be included after meeting all of the following:

The diagnostic criteria for PD (24) and experiencing an acute episode.Age 14 to 35 years old.4 ≤ pain visual analog scale (VAS) score ≤9.Have not received acupuncture treatment or taken analgesic drugs after this episode.Voluntary participation in this study and signed informed consent, with informed family consent required for those under 18 years of age.Have not participated in other PD studies.

### Exclusion criteria

Participants will be excluded if they have any of the following:

Combined severe life-threatening primary diseases and other acute abdominal pain.With severe anxiety, depression, insomnia, and other psychiatric disorders.Are afraid of acupuncture, do not cooperate with treatment, or are prone to acupuncture dizziness.

### Withdrawal criteria

Cases that do not meet the inclusion criteria or are mistakenly included should be excluded.Patients whose studies are terminated due to severe adverse events or complications, making further treatment inappropriate.Choose to withdraw from their participation in the study.

### Randomization and blinding

Participants will be randomly allocated to either the Acupuncture group or the Sham acupuncture (SA) group in a 1:1 ratio. Random numbers will be generated using SPSS 28.0 (IBM, Chicago, IL, USA, authorization Code: f56b44b8d8e3562ad8a2) by an independent statistician. Randomization information will be placed in opaque sealed envelopes and kept by personnel not involved in the study. Participants will be randomly assigned to different groups and treated in separate rooms to avoid communication. At the end of treatment, the success of the blinding will be assessed using a blinding questionnaire. Two experienced and licensed acupuncturists will participate in the treatment. The two acupuncturists will participate in either the needling group or the sham needling group. This design minimizes the risk of bias from treatment assignment information. To minimize potential bias, the acupuncturists will have no knowledge of the study results and will not be involved in outcome assessment or data analysis. Participants, outcome assessors, and statistical analysts will be unaware of group allocation.

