### Operation

Prior to the procedure, participants will be guided to lie in a supine position, ensuring full exposure of the acupoints. Subsequently, a licensed acupuncturist with a minimum of 3 years of experience will conduct the routine disinfection process. The procedure will then commence.

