### Acupuncture group

For participants in the Acupuncture group, PSD and disposable acupuncture needles will be used. After removing the sticker on the base, disposable acupuncture needles are introduced to expose the tips, and the skin is disinfected, the PSD is attached to the acupuncture points, and the acupuncture needles are stuck into the skin for treatment, and all acupoints are gently and straightly pierced by 20 to 30 mm. Lifting and twisting technique, will be employed to elicit the “Deqi” sensation. During the treatment session, a proficient research assistant will promptly gather VAS scores from the subjects at 0–1, 2, 4, 6, 8, and 10 min following the initiation of treatment. The data collection table is shown in Table 2.

**Table 2 tab2:** The data collection table.

Use a 10 cm VAS scale with a moving scale between 0 and 10 on the front and a number from 0 to 10 on the back, with 0 being no pain and 10 being the most painful. Please state your pain level according to the following scale.  VAS scale (0–10 points) 0: no pain; 1–3: light pain; 4–6: moderate pain; 7–10: severe and unbearable pain.

Projects	Before treatment	Treatment				
	0 min	2 min	4 min	6 min	8 min	10 min
Pain VAS score						

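### As most naturally read, each of the two acupuncturists treats only one arm, so practitioner and treatment are confounded and the claim that this minimises bias is not supported

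*Protocol article*

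**What the plan says.** All of the relevant text is in the protocol article.

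- Randomization and blinding fixes the number of practitioners: "Two experienced and licensed acupuncturists will participate in the treatment". It continues: "The two acupuncturists will participate in either the needling group or the sham needling group". The next sentence gives the reason: "This design minimizes the risk of bias from treatment assignment information".
- The same section describes allocation and setting: "Participants will be randomly allocated to either the Acupuncture group or the Sham acupuncture (SA) group in a 1:1 ratio", and "Participants will be randomly assigned to different groups and treated in separate rooms to avoid communication". It also keeps the acupuncturists out of outcome assessment and data analysis.
- Operation sets a qualification standard: "a licensed acupuncturist with a minimum of 3 years of experience will conduct the routine disinfection process".
- Sham acupuncture group says that, apart from the blunt needle and the absence of penetration, the procedure matches the real arm.
- Primary outcome is the proportion of participants whose VAS falls by at least half at 10 minutes. Participants mark the VAS themselves, during and at the end of the single session.

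No section says that either acupuncturist works in both arms or that allocation is balanced by acupuncturist. The limitations listed in the Discussion do not mention the point.

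**The concern.** Randomisation makes the patients in the two arms comparable. It does not make the people who treat them comparable. If one acupuncturist gives all the real treatments and the other all the sham treatments, the arms differ in needling and also in one individual's manner, confidence, suggestion and pace. The sham control exists to isolate needling, and this arrangement undoes part of that.

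The outcome is exposed to such effects: it is self-reported pain, taken over 10 minutes while the practitioner's influence is at its most direct. The bias could run either way.

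The stated rationale does not rescue the arrangement. One procedure penetrates and manipulates and the other only touches the skin, so whoever performs it knows which it is. A fixed split conceals nothing from the acupuncturists. It only tells each of them the arm of every patient in advance.

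This cannot be left to an analysis plan, because no analysis can separate two factors that always change together.

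**Working it through.** **Step 1: the plan's own figure.** Inputs from Sample size: mean VAS changes 4.21 and 2.15, SD 1.0, margin 1.3, one-sided alpha 0.025, power 90%, ratio 1. The standard form is n = 2(1.960 + 1.282)² × 1.0² / (4.21 − 2.15 − 1.3)² = 2 × 10.507 / 0.76² = 36.4 per arm. The plan states 36, which agrees to rounding. Then 36 / 0.92 = 39.1, hence 40 per arm. (The formula as printed squares the term 1 + 1/k and would give 72.8; that is a separate matter.)

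**Step 2: can arm and practitioner be separated?** Take a model with an intercept, an arm indicator and a practitioner indicator for 80 participants.

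- One practitioner per arm: the two indicators are the same column. The design matrix has rank 2 of 3, so only the sum of the two effects can be estimated.
- Both practitioners in both arms, 20 + 20 each: rank 3 of 3. An additive practitioner effect cancels from the arm comparison and can be adjusted for.

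This result needs no assumption about the size of the practitioner effect.

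**Step 3: illustration on mean VAS change.** Assumptions: residual SD 1.0 (the plan's figure), 36 per arm, no acupuncture effect, and a practitioner intraclass correlation (ICC) that the documents do not give.

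- Practitioner variance: τ² = ICC / (1 − ICC)
- Sampling SE of the arm difference: √(2/36) = 0.236
- Extra SD from one practitioner per arm: √(2τ²)
- Total SD: √(0.236² + 2τ²)
- True two-sided error of the nominal 5% test: 2 × [1 − Φ(1.96 × 0.236 / total SD)]

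| Assumed ICC | Extra SD (cm) | Total SD (cm) | True error, 36 per arm | True error, 40 per arm |
|---|---|---|---|---|
| 0.01 | 0.14 | 0.28 | 9.3% | 9.8% |
| 0.02 | 0.20 | 0.31 | 13.7% | 14.6% |
| 0.05 | 0.32 | 0.40 | 24.9% | 26.6% |

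The error rises from 36 to 40 per arm: the sampling part shrinks as n grows, while the practitioner part stays.

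**Step 4: illustration on the binary primary outcome.** With 40 per arm and no needling effect, suppose the practitioner alone moves the responder rate (assumed values). At 30% against 40%, about 15% of trials would be significant in favour of acupuncture; at 30% against 50%, about 45%. The nominal rate in that direction is 2.5%.

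**Step 5: cost of crossing in power.** On the plan's inputs, power is 89.7% at 36 per arm and 92.5% at 40 per arm. Crossing two existing practitioners requires no change to these sizes.

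**The case against.** **The sentence is loose.** It could mean that either practitioner may work in either group, and the Discussion uses the plural when it describes those who apply the blunt needle. A reader might infer that the protocol states outright that one person gives all real and the other all sham treatments. It does not. But there are exactly two practitioners and two groups, and the following sentence defends the arrangement as a deliberate design, so one per arm remains the more natural reading. The plural may be generic, and the section on the sham arm uses the singular. If the other meaning was intended, the sentence still has to be rewritten.

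**Practitioner differences are limited.** Both are licensed and experienced, and acupoints, device and procedure are shared apart from the needle and penetration. This stands as mitigation. It makes a large practitioner effect less likely but does not separate it from treatment.

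**The illustrated effects are small beside the expected one.** Against the planned difference of 4.21 − 2.15 = 2.06 cm, the extra SDs of 0.14, 0.20 and 0.32 cm are about 7%, 10% and 16%. This also stands: at those ICCs, practitioner alone would not plausibly produce the anticipated result. The exposure is greatest if the observed difference is modest.

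**Crossing has its own risk.** One person delivering both procedures may behave differently with each. That is true, but knowledge of allocation is present under the split as well. Crossing leaves that problem where it is and removes the additive difference between persons.

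**Assessor blinding.** The protocol says: "Participants, outcome assessors, and statistical analysts will be unaware of group allocation". It also says: "During the treatment session, a proficient research assistant will promptly gather VAS scores from the subjects". A reader might infer that the assistant can tell the arm from who is treating. The documents do not establish this. Participants mark an unnumbered line themselves under standard instructions, and an assistant at the bedside might recognise the technique whoever performs it. Crossing would not cure that, so it forms no part of this point.

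**Conclusion.** The concern holds on the most natural reading of Randomization and blinding. Practitioner and treatment are completely confounded, no analysis or added recruitment can undo it, the bias-minimising claim is unsupported, and the Discussion does not list it as a limitation.

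The confounding follows from the design alone. Its consequence in numbers does not: error rates of about 9%, 14% and 25% rest on assumed ICCs of 0.01, 0.02 and 0.05 for mean VAS change at SD 1.0 and 36 per arm. The responder-rate figures rest on equally assumed rates. A reader might take these as the trial's actual false-positive rate, or conclude that an expected benefit of 2.06 cm would be a practitioner artefact. The documents support neither, since they give no practitioner effect. What they support is that a difference between the arms could not be attributed to needling alone.

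**What to change.** 1. State plainly in Randomization and blinding which acupuncturist treats which arm.
2. Have both acupuncturists deliver both real and sham sessions, using the same script for interaction with the participant.
3. Balance allocation within acupuncturist, for example with a separate blocked envelope set for each.
4. Include acupuncturist as a factor in the primary analysis (for example a Mantel–Haenszel test or a logistic model for the responder rate) and in the VAS analyses.
5. Delete the sentence claiming that the present arrangement minimises bias.
6. For sessions already delivered under the split, or if crossing is no longer feasible, state the confounding as a limitation and restrict the conclusion: the comparison is of real acupuncture by one practitioner with sham by another.

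Cost: both acupuncturists are trained in both procedures and two envelope sets are kept. No staff or participants are added, and 40 per arm stands. The small downside is that each acupuncturist must keep the same manner across the two procedures.

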### Interventions

The intervention measures will be in accordance with the Consolidated Standards of Reporting Studies (25) and the Standards for Reporting Interventions in Clinical Studies of Acupuncture (26). Based on the previous literature and clinical experience (18, 27), we selected the dominant acupoints for the treatment of PD as the selected acupoints for this study, including SP4 (Gongsun), ST36 (Zusanli), LR3 (Taichong), SP6 (Sanyinjiao), ST41 (Jiexi), and SP8 (Diji), bilateral. All acupoints will be positioned based on the WHO Standard Acupuncture Point Locations 2010 (ISBN:1101119787117123327). The acupoints are located as shown in Figure 3 and Table 1.

**Figure 3 fig3:**
[figure not shown]
Location of acupoints.

**Table 1 tab1:** Location of acupoints.

Acupoints	Location
SP4 (Gongsun)	On the medial aspect of the foot, anteroinferior to the base of the first metatarsal bone, at the border between the red and white flesh.
SP6 (Sanyinjiao)	On the tibial aspect of the leg, posterior to the medial border of the tibia, 3 B-cun superior to the prominence of the medial malleolus.
SP8 (Diji)	On the tibial aspect of the leg, posterior to the medial border of the tibia, 3 B-cun inferior to SP9.
ST36 (Zusanli)	On the anterior aspect of the leg, on the line connecting ST35 with ST41, 3 B-cun inferior to ST35.
LR3 (Taichong)	On the dorsum of the foot, between the first and second metatarsal bones, in the depression distal to the junction of the bases of the two bones, over the dorsalis pedis artery.
ST4 (Jiexi)	On the anterior aspect of the ankle, in the depression at the center of the front surface of the ankle joint, between the tendons of extensor hallucis longus and extensor digitorum longus.

### Appliance selection

Acupuncture needle (Figure 4): use the Huatuo brand disposable acupuncture needles manufactured by Suzhou Medical Supplies Factory, China. Manufacturer’s license number: Su Food and Drug Administration (SFDA) of Machinery Production 20,010,020; Registration certificate number: 201622770970. The acupuncture needle specifications are 0.25 mm × 40 mm.Park Sham Acupuncture Device (PSD) (Figure 4): includes transparent guide tubes (Φ4 × 20 mm, Φ3 × 35 mm), double-sided tape (Φ1 × 15 mm), and opaque plastic bases (Φ4 × 15 mm, Φ5 × 10 mm) sourced from Suzhou Medical Supplies Factory, China (lot number 210401).Blunt needle (Figure 4): use retractable stainless steel blunt needles (0.25 × 40 mm), sourced from Suzhou Medical Supplies Factory, China (lot number 210401).

**Figure 4 fig4:**
[figure not shown]
Park sham acupuncture device.

### Operation

Prior to the procedure, participants will be guided to lie in a supine position, ensuring full exposure of the acupoints. Subsequently, a licensed acupuncturist with a minimum of 3 years of experience will conduct the routine disinfection process. The procedure will then commence.

### Acupuncture group

For participants in the Acupuncture group, PSD and disposable acupuncture needles will be used. After removing the sticker on the base, disposable acupuncture needles are introduced to expose the tips, and the skin is disinfected, the PSD is attached to the acupuncture points, and the acupuncture needles are stuck into the skin for treatment, and all acupoints are gently and straightly pierced by 20 to 30 mm. Lifting and twisting technique, will be employed to elicit the “Deqi” sensation. During the treatment session, a proficient research assistant will promptly gather VAS scores from the subjects at 0–1, 2, 4, 6, 8, and 10 min following the initiation of treatment. The data collection table is shown in Table 2.

**Table 2 tab2:** The data collection table.

Use a 10 cm VAS scale with a moving scale between 0 and 10 on the front and a number from 0 to 10 on the back, with 0 being no pain and 10 being the most painful. Please state your pain level according to the following scale.  VAS scale (0–10 points) 0: no pain; 1–3: light pain; 4–6: moderate pain; 7–10: severe and unbearable pain.

Projects	Before treatment	Treatment				
	0 min	2 min	4 min	6 min	8 min	10 min
Pain VAS score						

### Sham acupuncture group

For participants in the SA group, PSD and blunt needle will be used. During the procedure, the acupuncturist will have blunt needles touching the skin without penetrating the surface, the participants will feel a slight tingling sensation. The rest of the operation is the same as the Acupuncture group.

